## Abstract

**Background:**

Childhood tuberculosis continues to be a major public health problem. Although the visibility of the epidemic in this population group has increased, further research is needed.

**Objective:**

To design, implement and evaluate an integrated care strategy for children under five years old who are household contacts of bacteriologically confirmed pulmonary tuberculosis patients in Medellín and the Metropolitan Area.

**Methods:**

A quasi-experimental study in which approximately 300 children who are household contacts of bacteriologically confirmed pulmonary tuberculosis patients from Medellín and the Metropolitan Area will be evaluated and recruited over one year. A subgroup of these children, estimated at 85, who require treatment for latent tuberculosis, will receive an integrated care strategy that includes: some modifications of the current standardized scheme in Colombia, with rifampicin treatment daily for four months, follow-up under the project scheme with nursing personnel, general practitioners, specialists, professionals from other disciplines such as social work, psychology, and nutritionist. Additionally, transportation and food assistance will be provided to encourage treatment compliance. This strategy will be compared with isoniazid treatment received by a cohort of children between 2015 and 2018 following the standardized scheme in the country. The study was approved by the CIB Research Ethics Committee and UPB. ClinicalTrials.gov identifier NCT04331262.

**Discussion:**

This study is expected to contribute to the development of integrated care strategies for the treatment of latent tuberculosis in children. The results will have a direct impact on the management of childhood tuberculosis contributing to achieving the goals proposed by the World Health Organization's End TB Strategy.

**Trial registration:**

ClinicalTrials.gov identifier NCT04331262. Implementation of an Integrated Care Strategy for Children Contacts of Patients with Tuberculosis. Registered 2 April 2020.

**Supplementary Information:**

The online version contains supplementary material available at 10.1186/s12887-022-03798-x.

## Background

Tuberculosis (TB) in childhood is considered a public health emergency, particularly in developing countries [1], where it accounts for approximately 15% of TB cases [2, 3]. This form of the disease remains relatively ignored, mainly because of the major diagnostic challenges and low priority given by TB control programs. In 2012 the WHO began to publish data on the incidence of TB in children under 15 years of age separated from adults, showing the need to give more importance to childhood TB [4].

Compared to adults, children respond differently to the disease. This has important implications for prevention, diagnosis, and treatment. In addition, children living in close contact with bacteriologically confirmed pulmonary TB patients are at particular risk of infection (50%) and TB disease (8.5%), and progression from primary *M. tuberculosis* infection to disease, especially infants and children under five years of age. This makes them a target group for the treatment of latent TB infection (LTBI). Likewise, much of the postprimary TB is due to cases of reactivation of childhood-acquired infections [3, 5–12]. However, children who are household contacts of pulmonary TB patients do not receive proper care in the national TB control programs [3]. In 2020, the WHO reported that in Colombia, 38% of children under five years who were in household contact with bacteriologically confirmed TB patients were on treatment for LTBI [13].

The WHO recognizes the importance of identifying the best strategies to trace contacts, especially in children, and researching the best-tolerated TB preventive treatment regimens compared to those currently recommended [14, 15]. This highlights the need for studies on the identification of strategies to improve adherence to TB preventive treatment in children, the reporting and management of child contacts, identification of barriers reports including the private sector, access to health services and integrated services, and implementation/operational research on the use and impact of the newly developed integrated treatment decision algorithms [15].

The best-studied regimen for LTBI treatment is isoniazid 10 mg/kg per day, not exceeding 300 mg per day, in single doses for 12 months [16]. This regimen is almost 100% effective in children and protects them for at least 30 years [16, 17]. Most authorities recommend at least nine months of preventive treatment in children [16], but at least six months of continuous medication appears to be necessary to achieve a significant reduction in the risk of developing TB [18].

The 2020 WHO LTBI treatment guidelines recommend other treatment regimens with shorter duration and equal efficacy even for children, which could favor higher treatment completion rates [19]. These include rifampicin for four months and rifampicin plus isoniazid for three months. This scheme is already being used in some countries [20, 21]. However, the current recommendation for the treatment of latent TB in Colombia is still isoniazid, and recently, a scheme of 12 weekly doses of isoniazid and rifapentine exclusively for patients with HIV infection has been implemented [22].

To achieve the goals set by the WHO in its "End TB" strategy [23], it is necessary not only to fight active TB but also to address LTBI with effective strategies. Therefore, research on LTBI is also needed. Important aspects that have been identified comprise improvement of diagnostic tests and test performance for LTBI, shorter and better-tolerated treatment options, the study of efficacy and side effects of some drugs, especially in children, duration of protection of preventive treatments in high prevalence conditions, the benefit of liver enzyme monitoring, adherence and treatment completion, evidence of the effectiveness of context-specific interventions to improve adherence and treatment completion depending on the availability of resources, health system infrastructure, the use of "digital health", cost-effectiveness studies of LTBI treatment, programmatic management, the burden of LTBI in different at-risk populations, including community-based approaches, implementation of home-based models, the development of tools to facilitate the monitoring and evaluation of programmatic management of LTBI [19].

Therefore, it is necessary to propose an intervention strategy for the integrated care of children who are contacts of pulmonary TB patients. This would allow quick identification of children with active TB and timely treatment for LTBI as a preventive strategy for active TB [19].

This study will show the capability of a new comprehensive care strategy to prevent the development of TB in children who are contacts of bacteriologically confirmed pulmonary tuberculosis patients. The new strategy includes patient-centered care, based on primary health care, with a multidisciplinary approach, a less extensive treatment scheme, and incentives to favor LTBI treatment compliance and completion. The data gathered in this study can contribute to updating the current TB guidelines in Colombia and support updated WHO guidelines with stronger evidence.

### Study objective

To design, implement and evaluate an integrated care strategy for children under five years old who are household contacts of bacteriologically confirmed pulmonary tuberculosis patients in Medellín and the Metropolitan Area.

## Methods

### Study design

This quasi-experimental study will compare the outcomes of the implementation of two treatment strategies for LTBI in children in Medellín and the Metropolitan Area (Valle de Aburrá), Antioquia, Colombia. The intervention cohort will receive an integrated care strategy, which consists of diagnostic tests, the supply of a scheme treatment with daily rifampicin for four months, active monitoring, permanent education and contact with the parents and/or guardians. In addition, social, psychological, and nutritional assistance will be provided, with a 12-month follow-up. The control group will be the historic 2015 to 2018 cohort who received the standard care protocol, with a 9-month scheme of isoniazid [24].

This protocol was conceived following the Standard Protocol Items: Recommendations for Interventional Trials (SPIRIT) guidelines [25] (supplement 1).

### Study setting

The children will be clinically assessed, at first, at *Corporación para Investigaciones Biológicas* (CIB), a research and healthcare facility located in Medellín, in a consulting room adapted for clinical and epidemiological purposes. The diagnosis of active TB will be ruled out, and the diagnosis of LTBI will be confirmed. Treatment initiation and monthly clinical monitoring of treatment adherence, and possible side effects will be conducted at the same location. Similarly, the immune response assessment (tuberculin skin test-TST, and Interferon Gamma Release Assay-IGRA), blood samples, social, psychological, and nutritional evaluation of the participants as well as the 12-month clinical visit after the initial assessment will be carried out at the same facility.

Chest radiography (including standardized reading) and liver function analysis will be performed at the *Pablo Tobón Uribe Hospital*; when active TB needs to be ruled out, microbiology samples (induced sputum and gastric juice aspirate) will be obtained at the *Hospital Infantil Concejo de Medellín*. These samples will be tested with smear, culture, and Xpert MTB/RIF Ultra.

### Study population

The population will be the children under five years who are household contacts of bacteriologically confirmed pulmonary TB patients from Medellín and the Metropolitan Area, notified to the surveillance system during 2021 and 2022, for whom LTBI treatment is indicated. The sampling method is nonprobabilistic since TB household contact children will be recruited as new cases (incidents) of smear-positive confirmed pulmonary TB appear in Medellín and the Metropolitan Area.

### Sample size

According to previous studies, it is estimated that approximately 250 to 300 children who are household contacts of bacteriologically confirmed pulmonary TB patients from Medellín and the Metropolitan Area will be assessed for one year, with an estimated proportion of infection of 73.5%. The complete intervention of the integrated care strategy (with medication, incentives, and active follow-up) will be provided to children who require treatment for LTBI and who will also be selected incidentally, according to their willingness to participate. Considering the 59% isoniazid treatment adherence in the 2015–2018 cohort, adherence with the proposed strategy around 80%, 95% confidence, and 80% power, it is estimated that 75 children will be required in the proposed comprehensive care strategy (Epidat V 4.2). An additional 10% will be estimated due to lost to follow-up, therefore the total number of children to enter the integrated care strategy will be 85.

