### Outcomes

The primary outcome is treatment compliance, defined as the proportion of children who completed the treatment.

The secondary outcome is adverse events, defined as the proportion of children who presented any reaction during treatment.

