Subsequently, in the same city of Colombia in 2012, a study was conducted on children under five years living with patients with bacillary pulmonary TB. It was found that 28.6% children who were contacted by telephone had been adequately studied (with chest X-ray and TST); for children who attended clinical evaluation, the prevalence of active TB was 7.9%, and only 19.4% received treatment for LTBI. Given that most of the household contact children were not adequately studied and therefore did not receive the indicated treatment, there was no significant impact on the decrease in the incidence of TB in these children with respect to the cohort study conducted between 2005 and 2009 [44].

Considering those findings, in 2015, a cohort study in Medellín, Bello and Itagüí, Colombia was started, with a before-after design and a two-year follow-up of children under five years of age who were household contacts of pulmonary TB patients to analyze the effectiveness of LTBI treatment with nine months of isoniazid as recommended by the national TB program, by comparison with children from a 2005–2009 cohort who did not receive treatment. The treatment cascade showed that from 329 children who met the inclusion criteria, 74% were assessed, 66% started treatment, 45% received LTBI treatment for at least six months, and 23.1% for nine months. The qualitative approach allows us to understand the complexity that underlies the effectiveness of LTBI treatment. This can be summarized in three categories: daily life and conditions of possibility for children exposed to TB and their families (including forced migration); the Colombian health system does not guarantee real access to TB diagnosis and treatment; and perceptions and social constructions around TB (TB remains as a stigma) [24]. Considering these findings, the research team proposed the present protocol study addressing some of the issues aiming to tackle the treatment completion barriers by an integrated care strategy for children exposed to TB.

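### The 59% control adherence behind the sample size matches no figure in the plan's own 2015–2018 cascade, and the primary outcome does not say which isoniazid duration or denominator counts as completion

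*Protocol article*

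**What the plan says.** The Sample size section of the protocol article takes its control rate from the historical cohort and sets it against the rate expected under the new strategy: "Considering the 59% isoniazid treatment adherence in the 2015–2018 cohort, adherence with the proposed strategy around 80%, 95% confidence, and 80% power". From this, "it is estimated that 75 children will be required in the proposed comprehensive care strategy (Epidat V 4.2"). It gives no numerator, denominator or duration for the 59%, and no number of controls.

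Study design and Standard of care describe the controls as the 2015–2018 cohort on a nine-month isoniazid regimen; Study design cites reference 24 for it. The Discussion, citing the same reference, follows 329 children who met that study's inclusion criteria. It reports that 74% were assessed and continues: "66% started treatment, 45% received LTBI treatment for at least six months, and 23.1% for nine months".

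Under Outcomes: "The primary outcome is treatment compliance, defined as the proportion of children who completed the treatment". No duration is attached to the isoniazid cohort, and the base of the proportion (eligible, assessed or started) is not named. Data analysis plans a difference in compliance proportions between the two cohorts with 95% confidence.

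**The concern.** The planning rate and the cascade describe the same cohort but do not agree. The cascade offers several readings of completion that lie far apart, and 59% is none of them. Someone using the plan therefore cannot tell which historical rate the new strategy has to beat.

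Two things are at stake. The first is the stated power, which depends strongly on that rate. The second is the credibility of the result. The comparison is not randomised and the historical results are already known. If the completion threshold for the controls stays open until the new data are in, the comparator can be chosen with both sets of results in view.

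**Working it through.** **1. Reproducing the plan's figure.** Inputs from Sample size: p1 = 0.80, p0 = 0.59, 95% confidence, 80% power. Sidedness and allocation are not stated; two-sided and 1:1 are assumed. With p̄ = 0.695 and pooled variance under the null:

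n = [1.96·√(2·0.695·0.305) + 0.8416·√(0.80·0.20 + 0.59·0.41)]² / 0.21² = (1.276 + 0.534)² / 0.0441 = 74.3, so 75 per group.

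The 75 follows from its inputs.

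**2. Looking for 59% in the cascade.** Counts from the Discussion: assessed 0.74 × 329 ≈ 243; started 0.66 × 329 ≈ 217; at least six months 0.45 × 329 ≈ 148; nine months 0.231 × 329 ≈ 76.

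| Denominator | At least six months | Nine months |
|---|---|---|
| Eligible (329) | 45% | 23.1% |
| Assessed (243) | 45/74 = 60.8% | 23.1/74 = 31.2% |
| Started (217) | 45/66 = 68.2% | 23.1/66 = 35.0% |

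Nine-month completion among those who reached six months is 23.1/45 = 51.3%. The nearest value is six months among assessed children. Taking the published percentages at the limits of their rounding, it runs from 44.5/74.5 = 59.7% to 45.5/73.5 = 61.9%, so 59% is still not reached. That denominator also includes children who never started.

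**3. Power with 80% in the new cohort, two-sided 5%.**

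Power = Φ[(|p1 − p0| − 1.96·s0)/s1], where s0 = √[p̄(1−p̄)(1/n1 + 1/n0)], with p̄ weighted by group size, and s1 = √[p1(1−p1)/n1 + p0(1−p0)/n0].

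- p0 = 59%, 75 v 75: (0.21 − 1.96·0.0752)/0.0732 = 0.86, power 80%.
- p0 = 61%, 75 v 75: power 73%.
- p0 = 35%, 75 v 75: (0.45 − 1.96·0.0807)/0.0719 = 4.06, power above 99.9%.
- p0 = 68.2%, 75 v 75: (0.118 − 1.96·0.0715)/0.0709 = −0.31, power 38%.
- p0 = 68.2%, 75 v 217: power 49%; 85 v 217: power 54%.

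The 217 controls are an assumption: every starter in the cascade.

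**4. Effect on the conclusion.** Difference in percentage points with Wald 95% interval, 75 treated children v 217 assumed controls:

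| Observed in new cohort | v 35% | v 59% | v 68% |
|---|---|---|---|
| 60% | +25 (12 to 38) | +1 (−12 to 14) | −8 (−21 to 5) |
| 70% | +35 (23 to 47) | +11 (−1 to 23) | +2 (−10 to 14) |
| 75% | +40 (28 to 52) | +16 (4 to 28) | +7 (−5 to 19) |
| 80% | +45 (34 to 56) | +21 (10 to 32) | +12 (1 to 23) |

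In the first three rows the nine-month comparator shows a clear benefit and the six-month comparator does not. In the last row every comparator excludes zero, the 68% one only just.

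**The case against.** The strongest reply is that an untraceable figure is not thereby a false one. Standard of care limits the controls to children diagnosed with LTBI, while the cascade starts from all 329 who met the inclusion criteria and shows no diagnosis step. The 59% could belong to a diagnosed subgroup in the cited source, and a condensed article need not print every numerator. This stands: the documents do not show that 59% is wrong, and a reader who concludes that the study is simply underpowered goes too far. The discrepancy runs both ways, since a nine-month definition among starters leaves power ample.

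Two further inferences are tempting and should not be drawn. From "An additional 10% will be estimated due to lost to follow-up" one might conclude that lost children will be dropped from the new cohort's denominator while counting as failures in the old one. The text only enlarges the recruitment target; it does not say how losses are analysed in either cohort. One might also fault the 1:1 calculation because more historical children seem to be available. A larger control group would only raise power (93% at 59% with 75 v 217), and the number of controls is not given.

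The reply does not answer the open definition. The two passages give different figures for one cohort without explanation, and the stated primary outcome does not choose between readings that differ by more than 30 points among starters.

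**Conclusion.** The concern holds as a failure to reconcile stated figures, not as an arithmetic error. The stated 80% power is conditional on a comparator that the plan's cascade does not contain. Under the two definitions available among starters, power ranges from 38% to above 99.9% with 75 per group. The choice of definition settles the conclusion for observed completion of roughly 60–75%, but not at the planned 80%.

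The power figures assume a two-sided 5% test and 80% true completion in the new cohort. The 49–54% range and the interval table also assume 217 controls. The cascade percentages are read as shares of the 329. If they were instead shares of the preceding step, six-month completion among starters would be 45%, which again is not 59%.

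Because this concerns the sole primary comparison, against controls whose results are already known, it should be settled before the cohorts are compared. Which isoniazid duration counts as complete is for the investigators; the documents do not settle it and this review does not choose.

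**What to change.** Reconcile Study design, Sample size, Standard of care, Outcomes and the Discussion cascade, and before analysis:

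- Fix one completion definition for both cohorts: a named denominator (for example, all children who started treatment), the duration threshold that the investigators choose for the isoniazid cohort, and the same handling of losses in each cohort.
- Report the other isoniazid duration as a prespecified sensitivity analysis.
- Give the numerator, denominator and threshold behind the 59%, including any subgroup it comes from, or replace it with the rate that matches the chosen definition.
- State how many historical controls enter the comparison, and restate power for 75–85 treated children against that number.

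The cost is revised wording and one recalculation, with no extra patients. The downside is that the restated power may be less favourable, markedly so under a six-month definition among starters.

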### Eligibility criteria

For the initial evaluation, we will include all children under five years, who are household contacts of a bacteriologically confirmed pulmonary TB patient, live in Medellín or the Metropolitan Area, have a TST response ≥ 5 mm or an IGRA (QuantiFERON®-TB Gold Plus—QFT Plus) positive, are asymptomatic and without clinical signs of active TB, have a normal chest X-ray, and the parents or legal guardian sign the informed consent. Additionally, those children who are in the immunological window period, which refers to the time between potential infection and when a test (i.e., TST or IGRA) can accurately be positive for the infection, will also be included. In this specific scenario, the immunological window period comprises two months from the last exposure to the patient, that is, two weeks after treatment initiation. Children who have contraindications of receiving rifampicin have symptoms or signs of active TB and that the disease has not been ruled out, a liver disorder background, contraindication for performing induced sputum, severe asthma and/or plans to move out to a city out of the study coverage area will be excluded. The study is not gender-based, and healthy volunteers are not accepted.

### Intervention

The intervention will be the integrated care strategy, in which the effects of interventions established in the regulations of the TB program at the national level will be observed, such as the diagnosis and administration of treatment for LTBI in children who are household contacts of pulmonary TB patients. with three main modifications: the supply of daily oral rifampicin (oral suspension) in a four-month self-administered scheme, incentives such as transport and food assistance and the multidisciplinary support. In addition, immune response tests will be performed to measure interferon-gamma production levels (QuantiFERON®-TB Gold Plus—QFT Plus test). This strategy should allow children to be assessed at a single site avoiding going through different institutions and levels of authorization. Integrated care should include a general practitioner, a pediatrician, specialists such as a child infectious disease specialist, patient-centered care, and multipurpose visits. All children will be monitored for 1 year follow-up.

### Standard of care

The control group will be the historic 2015 to 2018 cohort of children with a diagnosis of LTBI who received a nine-month self-administered daily oral isoniazid scheme. The isoniazid comes in tablet form and must be diluted in water to be taken.

